### Trial design and setting

This is a double-blind, single-center, three-arm, non-inferiority study that will be conducted at the Surgical Endoscopy Center of the First Hospital of Lanzhou University from April 2022 to February 2023. Recruited participants will be randomly assigned to receive a combination of 3 L of PEG, 30 mL of hemp seed oil and 2 L of PEG, or 30 mL of hemp seed oil, 2 L of PEG, and 1000 mL of 5% sugar brine (Fig. 1).

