### Sample size

We calculated the expected sample size based on the preliminary extrapolation of the results of bowel preparation before the study began. According to the results of previous studies, when using 3 L PEG for bowel preparation, the qualified rate of bowel preparation was 80%. PEG was accepted as the standard preparation, and the aforementioned percentage was taken as a reference [18, 20, 37, 38]. Assuming the qualified rate of bowel preparation in this study is 85%, the alpha level was set to 0.05. When a sample size of 690 was calculated, a 5% difference between the three groups could be determined.

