### Recruitment, randomization, and blinding

Investigators trained for the study and authorized by the principal investigator will assess the candidates according to the inclusion and exclusion criteria on the day before the colonoscopy. After eligible participants are identified, written informed consent will be obtained from each eligible patient, next of kin, or legal representative. On the consent form, participants will be asked whether they agree to the use of their data and biological specimens. Participants will be asked to agree to the research team sharing relevant data with regulatory authorities as appropriate. Researchers should collect clinical data, including gender, age, weight, BMI, history of the previous colonoscopy, history of abdominal surgery, cardiovascular and neurological diseases, and long-term use of certain drugs.

Initially, the SPSS version 22.0 software will be used to generate random sequences, and these will be subsequently put in an opaque envelope. The independent statistical expert used a computer to generate random numbers, and the participants were assigned to the following 3 groups in a 1:1:1 ratio, numbered sequentially after random assignment: A, 3L PEG; B, 30 mL of hempseed oil and 2 L of PEG; and C, 30 mL of hemp seed oil, 2 L of PEG, and 5% sugar brine. Moreover, researchers, endoscopic physicians, and participants will all be blinded during the examination to eliminate bias as much as possible.

At the end of the study, unblinding will be carried out by the principal investigator. The first unblinding will be conducted to uncover the groups of participants, followed by statistical analysis to clarify the differences between the groups, and a second unblinding will be conducted to further clarify the specific groups. When an emergency, such as a serious adverse event, threatens the safety of a subject and the subject’s grouping must be known, an emergency unblinding would be conducted. The unblinding of the specific time, reason, and name of the executive of the emergency will be timely recorded.

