### Statistical analysis

In this study, we will adopt intent-to-treat and per-protocol methods to analyze all data. The basic information of patients is expressed by mean, median, and standard deviation. The chi-square test will be used to compare the categorical variables in the basic data of patients. In two independent samples, the Mann–Whitney *U*-test and Student’s test will be used for the comparison of continuous variables; the chi-square test will be used for the comparison of the main results; secondary outcomes will be compared using the chi-square test for categorical variables and Student’s *t*-test for continuous variables. All statistical analyses will be conducted with the 2-tailed test, and *P* < 0.05 will be considered statistically significant. We will make every attempt to collect complete information for all participants and avoid missing data. If necessary, missing data will be handled using multiple imputation. As no formal stopping rules have been specified for this study, no formal interim analyses are planned, and hence, no statistical testing will take place until the final analysis. All data were analyzed using SPSS 26 (SPSS Inc., an IBM Company, Chicago, IL).

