## Discussion

Colonoscopy can be used to visually diagnose intestinal diseases and reduce the incidence of colorectal cancer. The survey showed that the incidence of colorectal cancer in China increases with age [40]. Poor bowel preparation is an important factor that affects the failure of cecal intubation during colonoscopy and leads to a missed diagnosis of some polyps or lesions, which may warrant repeated colonoscopy [41]. There are many studies on modified bowel preparations; however, because of the existence of many adverse reactions or poor medical compliance and tolerance by patients, it is necessary to find safer and more effective bowel preparation methods [42–44]. Currently, many studies have demonstrated the laxative effect of hemp seed oil. However, there is no research on its use in bowel preparation, making it necessary to explore whether 30 mL of hemp seed oil can improve the bowel cleansing potential of PEG in bowel preparation.

We designed a randomized, double-blind, single-center clinical trial to investigate whether 30 mL of hemp seed oil can improve the potential of 2 L PEG for bowel preparation and whether a combination of 30 mL hemp seed oil and 5% sugar brine can reduce the required volume of PEG, as well as reduce the adverse reactions during bowel preparation.

The results of this trial will influence evidence-based decision-making for bowel preparation regimen prescriptions as it will be fundamental in providing reliable recommendations for bowel preparation regimens before colonoscopy.

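### The protocol applies one unadjusted P < 0.05 to a three-arm trial and names no primary contrast, so the error rate of the primary conclusion lies between 5% and about 12%, depending on an unstated choice

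*Protocol article*

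**What the plan says.** Trial design and setting declares the framework: "This is a double-blind, single-center, three-arm, non-inferiority study". Under Recruitment, randomization, and blinding, "the participants were assigned to the following 3 groups in a 1:1:1 ratio". The groups are A (3 L PEG), B (hemp seed oil with 2 L PEG) and C (as B, with 5% sugar brine). With 690 participants this is 230 per arm.

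The Statistical analysis section names the primary test in one clause: "the chi-square test will be used for the comparison of the main results". It does not say whether this is one three-group test or a set of two-group tests. The same sentence begins "In two independent samples", a phrase attached to the tests for continuous variables. The decision rule covers everything: "All statistical analyses will be conducted with the 2-tailed test", and a P value below "0.05 will be considered statistically significant". No adjustment, testing order or gate is given.

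The Sample size section sets alpha at 0.05 and says that "a 5% difference between the three groups could be determined", without naming a pair. It calls PEG the standard preparation, which suggests A as the reference but does not fix the contrasts. The end of the Introduction centres the aim on the sugar-brine regimen. The Discussion asks whether the oil improves 2 L PEG and, separately, whether the oil with "5% sugar brine can reduce the required volume of PEG".

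**The concern.** Two experimental regimens share most of their components and one control, and the protocol asks efficacy questions about both. Following the stated rule leads to one of two results. A 3x2 chi-square holds its 5% level, but a significant result says only that the three rates are not all equal. It does not say which regimen differs from 3 L PEG, and it cannot support a non-inferiority claim. Pairwise chi-square tests do identify a regimen, but each runs at the full 0.05 and nothing limits the chance that at least one is falsely positive.

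Because the contrast is not named, the headline comparison could also be chosen after the results are seen. The stated 0.05 would then not describe the error rate of the trial's primary conclusion.

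**Working it through.** **Inputs.** From the protocol: 690 participants, 1:1:1, so 690/3 = 230 per arm; control rate 80%; assumed rate 85%; two-sided 0.05; no interim analysis. Not stated: power, non-inferiority margin, contrasts.

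**1. The plan's own figure, 690.** It cannot be confirmed, because power and margin are missing.
- Superiority, 80% vs 85%, two-sided 0.05, 80% power: n = [1.96·√(2·0.825·0.175) + 0.842·√(0.8·0.2 + 0.85·0.15)]² / 0.05² = 906 per arm, or 2718 in total.
- Non-inferiority, same rates, assumed margin 5 points, one-sided 0.025, 80% power: n = (1.96 + 0.842)²·(0.16 + 0.1275) / (0.05 + 0.05)² = 226 per arm, or 678 in total.
- Other assumed values also come close: 85% vs 85%, margin 10 points and 85% power gives 687.

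The sample size therefore reveals neither the intended contrast nor any multiplicity allowance.

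**2. Error when all arms are equal (two-sided 0.05 per test).** For a pair, z = (p₁ − p₂) / √[2·p̄(1 − p̄)/230], with rejection if |z| > 1.96. This is the uncorrected 2x2 chi-square. Any two such statistics share an arm, so their correlation is 0.5 in absolute value.
- Two tests against control: 1 − P(|Z₁| ≤ 1.96 and |Z₂| ≤ 1.96), with correlation 0.5, gives 9.1%.
- All three pairs: the largest |z| times √2 is distributed as the range of three standard normals, so 1 − P(range ≤ 1.96·√2 = 2.77) gives 12.2%.
- One 3x2 chi-square on 2 degrees of freedom: 5% by construction.

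Two million simulated trials of 230 per arm agree:

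| Procedure | Rate 80% | Rate 85% |
|---|---|---|
| One pair | 5.0% | 5.0% |
| B vs A and C vs A | 9.0% | 9.1% |
| All three pairs | 12.1% | 12.1% |
| 3x2 alone, or as a gate before pairs | 5.0% | 5.1% |
| Bonferroni, two tests at 0.025 | 4.7% | 4.7% |
| Bonferroni, three tests at 0.05/3 | 4.3% | 4.5% |

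Treating the tests as independent would give 1 − 0.95³ = 14.3% for three pairs. The 12% already allows for the shared arms.

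**3. Error on the non-inferiority scale.** Assume a 5-point margin, A at 80%, and B and C both exactly at the margin (75%). A claim is made when the lower 95% confidence limit for the difference exceeds −5 points, nominally one-sided 2.5%. The two statistics correlate at (0.8·0.2) / (0.8·0.2 + 0.75·0.25) = 0.46. Then 1 − P(Z₁ ≤ 1.96 and Z₂ ≤ 1.96) = 4.6%, and simulation gives 4.7% for either regimen. The result depends little on the assumed margin: correlation 0.5 gives 4.5%, and the ceiling is 2·2.5% = 5%.

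**The case against.** A reader might infer that the false-positive rate simply is 12% instead of 5%. The protocol does not support that. The figure needs all three pairs to be tested, unadjusted and ungated. The reference to two independent samples governs the continuous-variable tests, and the sample-size wording about three groups fits a single 3x2 test, which holds 5%. If that 3x2 test gated the pairs, the chance of any false result with all arms equal would also stay at 5%. Nor is 12% the error of a non-inferiority claim, which arises at the margin and normally from B vs A and C vs A only.

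Three further points have weight. The Discussion gives the two regimens partly different questions, and whether distinct arms with a shared control need joint error control is partly a matter of judgement. The Introduction and the Sample size section hint at C as the focus and A as the reference. And a condensed article may leave testing order and adjustment to an analysis plan not shown here.

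These points make the 12% conditional, but they do not settle the matter. The blanket P < 0.05 is positive text, and any later adjustment would have to depart from it. No gate is mentioned, the hints do not designate a contrast, and the one reading that keeps 5% cannot deliver the declared non-inferiority conclusion.

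**Conclusion.** The point holds as an unfixed choice with a bounded consequence. One unadjusted two-tailed threshold is applied to three arms and no primary contrast is named. Depending on what is done, the chance of at least one false significant result with all arms equal is 5% (one 3x2 test, identifying no regimen), about 9% (two tests against 3 L PEG) or about 12% (all three pairs). The pairwise figures assume ungated, uncorrected tests with 230 per arm. They barely change between rates of 80% and 85%.

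Under the declared design, the chance of falsely declaring at least one regimen non-inferior is about 4.7% against a nominal one-sided 2.5%. That assumes a 5-point margin with both regimens lying exactly on it. The two-sample tests named in the Statistical analysis section suggest pairwise use but do not fix it for the primary outcome. The plan should be corrected; no particular error rate has been shown to apply.

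**What to change.** Before the first unblinding, state the following in the protocol:

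- The primary contrasts are B vs A and C vs A.
- The overall error is controlled either by a fixed testing order or by a Holm or Bonferroni adjustment. The order is for the sponsor to choose; the aim at the end of the Introduction would support C vs A first.
- Each contrast is tested by comparing the confidence limit for the difference with a pre-stated non-inferiority margin. The sponsor must supply and justify that margin, since the article gives none.
- C vs B and all secondary outcomes are reported as estimates with confidence intervals, without confirmatory claims.

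**Cost.** No extra patients are needed to write this down, but the margin has to be settled as well.

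With a fixed order, the second contrast is not confirmatory if the first fails. This could happen often: with an assumed 5-point margin and equal 80% rates, first-step power is Φ(0.05/√(0.32/230) − 1.96) = Φ(1.34 − 1.96), about 27%.

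With an adjustment, each contrast loses some power. For 80% vs 85% and the same assumed margin, the standard error is √(0.2875/230) = 0.0354. Power falls from Φ(2.83 − 1.96), about 81%, to Φ(2.83 − 2.24), about 72%, under Bonferroni at one-sided 0.0125. Holm loses less.

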### Study endpoints

#### Primary outcomes

The effect of intestinal preparation was regarded as the main outcome indicator and was scored using the Boston Bowel Preparation Scale (BBPS). As a commonly used clinical bowel preparation assessment scale, the BBPS score divides the large intestine into 3 segments (rectum and sigmoid colon, transverse colon and descending colon, ascending colon and cecum) and scores after adequate bowel preparation. Each intestinal segment was scored from 0 to 3 points, and the total score ranges from 0 to 9 points. The indications of scorings were as follows: 0 points, the entire intestinal mucosa cannot be observed due to irremovable solid or liquid feces; 1 point, parts of the intestinal mucosa cannot be observed due to the presence of stains, turbid liquid, and residual feces; 2 points, the intestinal mucosa is well observed, but a small amount of stains, cloudy liquid, and feces remain; and 3 points, the intestinal mucosa is well observed, and there are no residual stains, cloudy liquids, and stools [39]. In this study, the total score of BBPS score is > 5, and any intestinal segment ≥ 2 points can be considered satisfactory intestinal preparation.

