#### Secondary outcomes

Adverse reactions that occur during bowel preparation are the secondary outcome indicators of the study. We evaluated the interval between taking bowel preparation and the first bowel movement, the total number of bowel movements completed, time of cecal intubation, detection rate of polyps and adenomas, willingness to repeat the same bowel preparation, whether the protocol is tolerated (0 points for no discomfort; 1 point for mild discomfort; 2 points for ability to tolerate; 3 points for not being able to tolerate), and adverse events.

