### Rescue therapy

For participants with poor bowel preparation, the endoscopist will determine whether to continue colonoscopy. If colonoscopy cannot be performed because of insufficient bowel preparation, bowel preparation can be performed again free of charge. Moreover, in case of serious adverse reactions, the investigator will provide prompt and appropriate treatment based on the diagnosis and documents related to all treatment options.

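### Multiple imputation is the only stated missing-data rule, and nothing exempts Boston scale scores that are missing because the preparation failed

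*Protocol article*

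**What the plan says.** The Statistical analysis section sets the analysis populations: "In this study, we will adopt intent-to-treat and per-protocol methods to analyze all data". Its one rule for incomplete data is "If necessary, missing data will be handled using multiple imputation". No variable is exempted, and the reason for missingness plays no part.

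The Primary outcomes section rests the main result on the BBPS and defines success: "In this study, the total score of BBPS score is > 5, and any intestinal segment ≥ 2 points can be considered satisfactory intestinal preparation". The scale has a bottom category for a bowel that cannot be seen: "the entire intestinal mucosa cannot be observed due to irremovable solid or liquid feces".

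The Rescue therapy section covers a poor preparation. First, "the endoscopist will determine whether to continue colonoscopy". Then: "If colonoscopy cannot be performed because of insufficient bowel preparation, bowel preparation can be performed again free of charge". The Secondary outcomes section also expects some participants to fail on tolerability, with a score category of "3 points for not being able to tolerate".

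No section says how an examination that was not done, or not finished, because of poor preparation enters the primary endpoint. No section says which attempt supplies the BBPS when the preparation is repeated.

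**The concern.** Standard multiple imputation assumes that, given the variables in the model, an unscored participant resembles a scored one. That assumption fails when the score is absent because the bowel was too dirty to examine. Such an outcome is known and unfavourable, so there is nothing to impute. Filling it in from scored participants, most of whom succeed, would turn part of the known failures into successes.

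The repeat preparation raises a second, separate problem. If the BBPS recorded after it were used, the randomised regimen would be credited with the effect of extra preparation.

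The Trial design section calls the study a non-inferiority trial. In that setting, failures that are hidden more in one arm than in another can move the comparison that decides the trial.

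**Working it through.** **Inputs from the article.** Sample size section: 690 participants, 80% success with 3 L PEG, 85% assumed in this study, a 5-point difference. Allocation 1:1:1, so 690 / 3 = 230 per arm. The 230 and the 5 points serve only as a scale here. The article states no non-inferiority margin, so the 5-point planning difference is the only yardstick.

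**Inputs assumed.** The article gives no rate of, or reasons for, missing BBPS. I take a missing share m of 2% to 10% per arm and success p of 80% to 85% among those scored. I take every missing score to be a true failure, and the imputation model to hold no informative predictor of failure.

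**One arm.** Counting the missing as failures gives a success rate of p(1 − m). Imputation under missing at random gives about p. The overstatement is p − p(1 − m) = p × m.

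| m | Missing of 230 | Overstatement, p = 80% | Overstatement, p = 85% |
|---|---|---|---|
| 2% | 4.6 | 1.6 points | 1.7 points |
| 5% | 11.5 | 4.0 points | 4.25 points |
| 10% | 23 | 8.0 points | 8.5 points |

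For example, with m = 5% and p = 85%, the failure-counted rate is 0.85 × 0.95 = 80.75%, against 85% after imputation. About 11.5 × 0.85 = 9.8 of the 11.5 failures would be drawn as successes.

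If only a share f of the missing scores are failures, and the rest succeed at rate p, the overstatement falls to p × m × f. With m = 5% and f = one half, it is 2.0 to 2.1 points.

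**Between arms.** With the same p in both arms, the B − A difference shifts by p(m_B − m_A).

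- Equal missingness: 0. If p also differs (80% versus 85%) with 5% missing in each arm, the shift is 0.05 × 0.05 = 0.25 points, which is negligible.
- 3% in A, 6% in B: 0.03 × 0.80 = 2.4 to 0.03 × 0.85 = 2.55 points in B's favour.
- 2% in A, 8% in B: 0.06 × 0.85 = 5.1 points in B's favour.
- Reversing the arms reverses the sign.

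**Repeat preparation.** If the repeat score replaced the missing one and a share r of repeats succeeded, the overstatement would be m × r, at most m. The article gives no value for r.

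**The case against.** The strongest reply is that few failures will be missing at all. A dirty bowel that is viewed can be scored 0 or 1. If every segment must reach 2, which seems to be the intended meaning, one low segment settles failure without the other two. The endoscopist's decision whether to continue suggests that the bowel has often been seen already. Nothing says that a participant who does not finish the drink goes unexamined. This stands, and it limits the size. At p = 80% to 85%, m = 5% would mean that 5 / 24.0 = 21% to 5 / 19.25 = 26% of all failures went unscored, where 24.0 and 19.25 are 100 × [1 − p(1 − m)]. The upper end of the 2% to 10% range is therefore demanding.

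A second reply is that a good imputation model would use tolerance score, adverse events and bowel-movement data, all of which are collected. That could reduce the bias. The model may well sit in an analysis plan not shown, and its absence is no finding. But a better model still imputes an outcome that is already known.

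A reader might go further in four ways, none of which the article supports:

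- **That missing scores arise mainly from failed or intolerable preparation.** No reasons or frequencies are given. No-shows and withdrawals are possible, and eligibility already requires that participants can tolerate preparation.
- **That failures will be imputed as successes.** Imputation is probabilistic and applies only if needed.
- **That the rule favours the reduced-volume arms.** The Introduction argues that PEG is poorly tolerated partly because of the volume to be drunk. If intolerance drives missingness, the 3 L arm could lose more scores, and the bias would run against arms B and C.
- **That the imputation sentence brings in scores from the repeat preparation.** It does not. That gap comes from the Rescue therapy section alone.

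**Conclusion.** The point holds in a limited form. The article states one missing-data rule for all data and also describes a route by which the primary outcome goes missing because the treatment failed. Followed as written, the rule could treat a known failure as an unknown value, and the article does not rule out a score taken after a second preparation. The Primary outcomes, Rescue therapy and Statistical analysis sections need to be reconciled.

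The 1.6 to 8.5 point range depends wholly on assumed missing shares, on all missing scores being failures, and on an uninformative imputation model. It describes bias in a single arm's rate. Bias in the comparison needs unequal missingness, and neither its presence nor its sign can be read from the article. It is worth correcting because a difference of a few percentage points in missingness can use up about half of the planning difference or, at 2% versus 8%, all of it.

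**What to change.** For the primary intention-to-treat analysis, state that:

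1. A randomised participant counts as unsatisfactory if the first colonoscopy was not performed or not completed because of inadequate preparation, or if there is no BBPS because the assigned preparation was not completed for intolerance or an adverse reaction.
2. Where a BBPS from the first examination exists, it is used as observed, even if the participant tolerated the regimen badly. Failing such participants regardless of their score would override the endpoint definition and mix cleansing with tolerability, which is a separate secondary outcome.
3. The BBPS comes only from the first examination after the assigned regimen, never from a repeat preparation.
4. The reason for each missing BBPS is recorded in the case report form, before unblinding.
5. Multiple imputation is limited to BBPS missing for reasons unrelated to preparation, such as a cancelled appointment.

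A sensitivity analysis that varies the success rate among the imputed cases is optional.

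The cost is a few sentences of analysis wording and one case report form item. Clinical care is unchanged. Reported success rates may be slightly lower. No interim testing is planned, so the wording can be settled before the final analysis.
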